## Abstract

**Background:**

Deep brain stimulation (DBS) of the subthalamic nucleus (STN) is an established treatment for disabling motor symptoms of Parkinson’s disease (PD) that persist despite optimal pharmacological treatment. Currently, DBS is not performed if there is concomitant significant cognitive impairment based on concerns of cognitive deterioration, higher complication rate and less functional improvement. However, this has not been investigated so far.

**Methods:**

A single center, prospective, randomized, open-label, blinded end-point (PROBE design) pilot clinical trial is being performed. Patients are eligible for the trial if they have PD dementia (PDD), are able to provide informed consent, and experience disabling motor response fluctuations, bradykinesia, dyskinesia, or painful dystonia, despite optimal pharmacological treatment. In total 44 patients will be randomized to either STN-DBS accompanied by best medical treatment (DBS group) or to best medical treatment alone (BMT group). The primary outcome measure is the change from baseline to 30 weeks on the Movement Disorder Society—Unified Parkinson’s Disease Rating Scale part III score in a standardized off-drug phase. The main secondary outcome measures consist of scales assessing cognitive aspects of daily living, neuropsychiatric symptoms and impulsive compulsive disorders. Additional secondary outcome measures include motor signs during on-drug phase, dyskinesia, motor fluctuations, cognitive performance, (severe) adverse events, treatment satisfaction, and caregiver burden. Patients will be followed during 52 weeks after randomization.

**Discussion:**

The Deep Brain Stimulation for MOtor symptoms in patients with Parkinson’s disease DEmentia (DBS-MODE) trial directly compares the effectiveness and safety of DBS with BMT in patients with PDD.

**Trial registration:**

The DBS-MODE trial has been registered in the International Clinical Trial Registry Platform (NL9361) on the 24^th^ of March 2021 (https://trialsearch.who.int/Trial2.aspx?TrialID=NL9361).

**Supplementary Information:**

The online version contains supplementary material available at 10.1186/s12883-023-03142-5.

## Background

Parkinson’s disease (PD) is a neurodegenerative disorder that affects the motor, autonomic, cognitive, affective, and sensory systems [1]. Deep brain stimulation (DBS) of the subthalamic nucleus (STN) is an established treatment for disabling motor response fluctuations and dyskinesia that persist despite optimal pharmacological treatment [2]. After DBS surgery, patients with advanced PD generally have significant improvement of motor symptoms, functioning in daily living, and health-related quality of life (QoL). Cognitive impairment is an important and disabling feature of PD. Within ten years after diagnosis up to 70% of patients with PD will have developed PD dementia (PDD); meaning there is an obvious deficit in at least two cognitive domains impairing functioning in daily life [3, 4].

Currently, PDD is considered a relative contra-indication for treatment of motor symptoms with DBS [5]. There is a concern that DBS might worsen cognitive impairments and that the former generally routine procedure of the patient being awake during DBS surgery might be too burdensome for patients with dementia. Yet, the rationale to withhold these patients from DBS is weak and current literature even suggests otherwise. First, PD patients with mild cognitive impairment (MCI) treated with DBS do not experience a significant additional cognitive decline compared to patients who have not undergone DBS [6, 7]. The impact of DBS on cognition and development of delirium and psychosis in patients with PDD however is unclear. The current evidence consists of a case series, in which this did not seem to be an obvious issue [8]. In patients with PD who underwent DBS surgery of the nucleus basalis of Meynert aimed at improving cognitive symptoms, the risk of developing delirium and psychosis did not appear to be increased [9–11]. Second, the burden of DBS surgery has been significantly reduced now that DBS surgery of the STN under general anesthesia is becoming standard-of-care and seems equally effective for motor symptom control [12–14]. Lastly, the presence of dementia is not an absolute exclusion criterion for other (invasive) procedures, such as surgery after hip fracture and dialysis for end stage renal disease [15, 16].

The improvement in motor function with DBS in PDD patients is possibly similar to PD patients without dementia [8, 17]. However, this has never been formally tested in this population and hence this is the primary objective of this pilot trial. Our main secondary objective is to investigate possible changes in cognitive functioning and psychiatric symptoms following DBS compared with best oral medical treatment (BMT). The findings of this pilot trial will help determining the merits of conducting a future large-scale clinical trial to assess the clinical usefulness of DBS in PDD.

## Methods

### Study design

The study is a single center, prospective, randomized, open-label, blinded end-point (PROBE design) pilot clinical trial. The effectiveness and safety of STN DBS surgery with current standard practice of medical treatment will be assessed (Fig. 1).

**Fig. 1 Fig1:**
[figure not shown]
Flowchart of the DBS-MODE trial. Deep brain stimulation (DBS) group: treatment with DBS of the subthalamic nucleus and best medical treatment (BMT). BMT group: treatment with BMT

### Patients

Patients will be recruited from Amsterdam UMC, The Netherlands. Patients with PD and disabling motor symptoms who are referred to Amsterdam UMC for DBS screening and who have dementia will be asked to participate in the trial. In order to participate in this study, a subject must meet all of the following inclusion criteria: a) age 18 years and older; b) diagnosis of PD according to the clinical diagnostic criteria of the Movement Disorder Society (MDS) [18]; c) despite optimal pharmacological treatment, at least one of the following symptoms, that are severe enough to impair functioning in daily life independent of dementia: motor response fluctuations, dyskinesia, painful dystonia, or levodopa-responsive bradykinesia; d) diagnosis of probable or possible PDD according to the MDS clinical diagnostic criteria [3] (see supplementary Table 1); e) a life expectancy of at least two years; f) subject has decision capacity to give informed consent; g) subject provides written informed consent; h) regular contact with a caregiver, who has on average at least twice a week contact with the subject and also provides written informed consent for their own participation. Exclusion criteria are: a) any neurodegenerative disorder other than PD; b) previous neurosurgery for PD (*e.g.*, DBS, pallidotomy, thalamotomy); c) contraindications for DBS surgery, such as a physical disorder making surgery hazardous; d) Hoehn and Yahr stage 4 or 5 at the best moment during the day [19]; e) co‐existence of another abnormality or disorder, that causes cognitive impairment that may improve with specific treatment or that besides PDD is judged to contribute significantly to the cognitive impairment by the treating physician; f) current major depressive episode according to the fifth edition of the Diagnostic and Statistical Manual of Mental Disorders (DSM-5) [20]; g) current psychosis; h) other severely disabling condition; i) immobility during the greater part of the day not related to off-drug phase (*e.g.*, due to apathy); j) pregnancy, breastfeeding, and women of childbearing age not using a reliable method of contraception. Of importance, previous treatment with intrajejunal levodopa infusion or subcutaneous apomorphine infusion is not a reason for exclusion.

### Study procedures

Patients with PD and dementia who have been referred to Amsterdam UMC for DBS, will be informed about the study and will be asked to participate in the study. The research team will decide if patients are considered eligible based on the inclusion and exclusion criteria. Many patients with dementia are able to give informed consent [21, 22]. However, the assessment of the capacity to give informed consent will be done in advance at the discretion of an experienced neurologist from the study team. If a potentially eligible patient is considered not to be able to provide consent because he or she is mentally incompetent, the patient will not be included in the trial. In order to be eligible to participate in this study, it is necessary that the patient has an involved caregiver who will be present during the follow-up visits. Because the caregiver is partaking in the study, the caregiver also needs to sign an informed consent for his or her own participation. After written informed consent has been obtained, patients will be assessed in-hospital whether improvement in motor symptoms is considered likely by means of standardized on- and off-drug assessments. This will be done during Visit 1 along with the assessment of other study outcomes. The results of Visit 1 will be discussed during a multidisciplinary meeting, in which the DBS indication for the treatment of motor symptoms is discussed. This is similar to standard care. If patients are considered eligible, they will be randomized to treatment with STN-DBS and BMT (DBS group) or to BMT without the operation (BMT group).

### Randomization

In this trial, 44 patients will be randomized to the DBS group or BMT group in a 1:1 ratio. The randomization of the patients will be web-based and performed on Castor by using randomly permuted blocks with block sizes of 2 and 4 [23]. There is no stratification of randomization. Blinded assessment of the primary outcome (*i.e.*, Movement Disorder Society-Unified Parkinson’s Disease Rating Scale (MDS–UPDRS) part III during off-drug phase) will be performed by a blinded study team member. Because in bald patients and patients with short hair stigmata due to the DBS treatment may be visible, all patients will wear a head cover during the motor examinations at baseline and 30 weeks follow-up.

### Intervention

#### Deep brain stimulation surgery

Implantation of the DBS electrodes will be performed under general anesthesia with a stereotactic frame-based procedure. Target coordinates are obtained after fusion of an intraoperative cone-beam CT with a pre-operative 3-T MRI with the target planning. One-track microelectrode recordings are performed to confirm the dorsal and ventral border of the STN. After electrode implantation, the electrodes are connected via extension cables to a pulse generator that is implanted on the wall of the chest in the same surgical session. Confirmation of correct electrode placement is performed with a direct intraoperative CT-scan.

The pulse generator is connected to the electrodes. On average, patients are hospitalized for four days. Patients will regularly visit the outpatient clinic to adjust stimulation parameters and PD medication as part of the regular clinical routine. If necessary, caregivers may adjust the stimulation parameters with a DBS remote control after contacting the DBS team by telephone to minimize the burden of the patient. The protocol does not impose the use of DBS equipment from a particular manufacturer.

#### Best oral medical treatment

All patients will receive BMT, consisting of PD treatment according to current guidelines and can be adjusted accordingly. This includes all modes of medications (*e.g.*, levodopa, dopamine agonists, monoamine oxidase type B inhibitors, catechol-O-methyltransferase inhibitors, and amantadine), except advanced device-assisted treatments (*e.g.*, continuous intrajejunal levodopa infusion and subcutaneous apomorphine infusion) unless already initiated before inclusion. The referring treating neurologist will manage the medical treatment. If necessary, neurologists in Amsterdam UMC will advise the treating neurologist on how to optimize the medical treatment.

### Objectives

As previously mentioned, all objectives in this study serve to guide the conduct of a potential future larger-scale trial evaluating the clinical usefulness of DBS in PDD. The primary objective is to answer the following question: do patients with PDD who are suffering from disabling motor response fluctuations or dyskinesia experience a clinically relevant improvement in motor impairment during off-drug phase after treatment with DBS of the STN accompanied by BMT compared to BMT alone?

Our main secondary objective is to investigate the difference in cognitive impairment and psychiatric symptoms between the DBS group and the BMT group. Other secondary objectives include on-drug phase motor symptoms, functional health status, incidence of falls, use of PD medication, (serious) adverse events ((S)AEs), treatment satisfaction, caregiver burden and medical care use compared between the DBS group and BMT group.

### Outcome measures and assessment scales

#### Primary outcome measures

The primary outcome is the change from baseline to 30 weeks after randomization in MDS-UPDRS part III off-drug phase [24] compared between the DBS group and the BMT group.

#### Secondary outcome measures

The main secondary outcomes are: a) cognitive evaluation (Amsterdam iADL questionnaire – short version (A-IADL-Q-SV) [25]); and b) psychiatric assessment (Neuropsychiatric Inventory Questionnaire (NPI-Q) [26] and Questionnaire for Impulsive Disorders in Parkinson’s Disease (QUIP) [27]). For the main secondary outcome a composite outcome measure will be used. Fulfilling one or more of the criteria for this composite outcome measure is compatible with cognitive and/or psychiatric decline. Patients will fulfill the criteria for this composite outcome measure if at least one of the following applies: a) the post-operative A-IADL-Q-SV score is ≥ 2.50 points lower than the pre-operative score; b) regarding the NPI-Q: the post-operative severity score on one of the 12 items is ≥ 2 points higher than the pre-operative score or the post-operative total NPI-Q severity score is ≥ 4 points higher than the pre-operative score; or c) on the post-operative QUIP the patient fulfills the criteria for either an impulse control disorder (ICD), other compulsive behavior or compulsive use of medication when these criteria were not fulfilled pre-operatively. Additional secondary outcomes are: a) motor symptoms (*i.e.*, MDS-UPDRS part III in on-drug phase, MDS-UPDRS part II in both off-drug and on-drug phase, Clinical Dyskinesia Rating Scale (CDRS) [28], and motor symptom diary); b) cognitive evaluation (Montreal Cognitive Assessment (MoCA) [29]); c) functional health (Academic Medical Center Linear Disability Score (ALDS) [30], Modified Rankin Scale (MRS) [31], Hoehn and Yahr stage, and Clinical Global Impression of Change (CGI-C)); d) incidence of falls in the preceding three months; e) PD and psychiatric medication; f) (serious) adverse events ((S)AE, including but not limited to surgical complications, delirium, hospitalization, and admission in nursing home; g) caregiver burden (Zarit Burden Interview [32]); h) recruitment and retention rate; and i) medical care use, which will be estimated by the amount of additional medical care contacts (*i.e.*, outpatient clinic, inpatient clinic and telephone consultation). Other study parameters that will only be assessed in the DBS group are the occurrence of delirium in the postoperative phase (based on DSM-5 criteria) and treatment satisfaction. The manufacturers and types of DBS systems that are used will also be reported. For an overview of all assessments, see supplementary Table 2.

### Assessment visits

There are six prespecified assessment visits (Fig. 2); an inclusion visit (outpatient clinic), a baseline assessment (Visit 1—hospitalization), an assessment one week after surgery (Visit 2 – outpatient clinic), an assessment (of safety) 15 weeks after randomization (Visit 3 – telephone or outpatient clinic), an assessment of the primary and secondary endpoints 30 weeks after randomization (Visit 4—hospitalization), and an assessment of functional health status 52 weeks after randomization (Visit 5 – telephone or outpatient clinic). See supplementary Table 2 for the assessments performed at the different visits.

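### The DBS arm has earlier and more frequent study contact than the BMT arm, so the planned adverse-event comparison risks unequal ascertainment of non-serious, transient events

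*Protocol article*

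**What the plan says.** The Assessment visits section of the protocol article lists six prespecified visits. After the inclusion visit and baseline (Visit 1) they are:

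- Visits 2 and 3: "an assessment one week after surgery (Visit 2 – outpatient clinic), an assessment (of safety) 15 weeks after randomization (Visit 3 – telephone or outpatient clinic".
- Visit 4: "an assessment of the primary and secondary endpoints 30 weeks after randomization (Visit 4—hospitalization".
- Visit 5: week 52 after randomization, by telephone or in the clinic.

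Visit 2 is counted from surgery and the later visits from randomization. Study procedures states that BMT patients are not operated on.

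The section on DBS surgery adds two further sources of contact in the DBS arm: "On average, patients are hospitalized for four days", and "Patients will regularly visit the outpatient clinic to adjust stimulation parameters and PD medication as part of the regular clinical routine". Under Best oral medical treatment, "The referring treating neurologist will manage the medical treatment", with the trial centre advising where needed. How often that neurologist sees a patient is not stated.

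The Objectives section lists among the secondary objectives "use of PD medication, (serious) adverse events ((S)AEs), treatment satisfaction, caregiver burden and medical care use compared between the DBS group and BMT group".

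**The concern.** An adverse-event comparison is fair only if both arms have the same chance of having an event noticed and written down. Here the study team sees a DBS patient around surgery, a week later and at programming visits. A BMT patient may not be asked by the study until week 15, possibly by telephone. A short episode of confusion or a passing drug side effect in week 3 can be noted promptly in one arm and has to be remembered for 12 weeks in the other. The patients have dementia, and neither they nor the referring neurologist are blinded.

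Fear of cognitive deterioration and complications is the stated reason why DBS is withheld from these patients, and the pilot is meant to guide a larger trial. A spurious excess of minor events under DBS could be read as harm, and any real excess would be hard to separate from it.

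**Working it through.** **Plan's own figure.** The document gives no figure on adverse-event ascertainment, so there is none to reproduce.

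**Contacts counted from the text.** Prespecified study contacts after baseline:

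| | DBS | BMT |
|---|---|---|
| Up to and including week 15 | 2 (Visit 2, week 15) | 1 (week 15) |
| Up to week 52 | 4 (Visit 2, weeks 15, 30, 52) | 3 (weeks 15, 30, 52) |

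The surgical stay and the programming visits come on top in the DBS arm. The number of programming visits is not given.

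**Illustration of size.** None of these inputs is in the document:

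- Both arms have the same true event rate, constant over time.
- An event is recorded at the next scheduled contact with probability 0.5^(delay/h), where h is the recall half-life in weeks.
- Visit 2 asks about adverse events.
- Surgery takes place 2, 4 or 8 weeks after randomization, so Visit 2 falls in week 3, 5 or 9.
- BMT patients' contacts with their own neurologist count as zero.

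For an interval of L weeks that ends in a contact, the event-weeks captured are (h/ln 2) × (1 − 0.5^(L/h)).

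Worked case, h = 8 and surgery at week 4 (h/ln 2 = 11.54):

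- BMT, weeks 0-15 (L = 15): 11.54 × 0.727 = 8.40; 8.40/15 = 56%.
- DBS, weeks 0-15 (L = 5, then 10): 11.54 × (0.352 + 0.580) = 10.75; 10.75/15 = 72%.
- Ratio for weeks 0-15: 10.75/8.40 = 1.28.
- Weeks 15-30 are the same in both arms (8.40). Ratio for weeks 0-30: (10.75 + 8.40)/(8.40 + 8.40) = 1.14.
- Weeks 30-52 are also the same (L = 22: 11.54 × 0.851 = 9.83). Ratio for weeks 0-52: 28.97/26.62 = 1.09.

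Effect of Visit 2 alone; each range covers the three surgery dates:

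| Half-life | BMT capture, wk 0-15 | DBS capture, wk 0-15 | Ratio 0-15 | Ratio 0-30 | Ratio 0-52 |
|---|---|---|---|---|---|
| 4 wk | 36% | 49-55% | 1.38-1.55 | 1.19-1.28 | 1.13-1.18 |
| 8 wk | 56% | 67-73% | 1.20-1.30 | 1.10-1.15 | 1.06-1.10 |
| 12 wk | 67% | 76-81% | 1.14-1.20 | 1.07-1.10 | 1.04-1.06 |
| 26 wk | 82% | 88-90% | 1.06-1.10 | 1.03-1.05 | 1.02-1.03 |

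If every programming visit also elicited events, at an assumed spacing of 4 to 6 weeks, the weeks 0-30 ratio would be roughly 1.3 to 2.1 for half-lives of 4 to 12 weeks. I put little weight on this, because the document describes those visits as routine care and gives no frequency.

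**Second illustration, without a recall model.** Assume 95% detection under DBS, 85%, 70% or 50% under BMT, and a true risk of 40% in both arms. The observed risk ratio is 0.95/0.85 = 1.12, 0.95/0.70 = 1.36 or 0.95/0.50 = 1.90, and the spurious risk difference is 4, 10 or 18 percentage points. With 22 per arm, the probability that a two-sided 5% Fisher test rejects is 2.2% under equal detection, and 2.8%, 5.9% or 17.0% in these three cases. With equal detection the bias is zero.

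**The case against.** A reader might infer that the comparison is biased as planned. The document does not support that. Bias depends on how events are elicited and over what window. The article does not say, and it refers the visit content to a supplementary table that is not shown. If the week-15 contact recovers the whole interval equally well in both arms, there is no bias. This stands, and it is why the point is put as a risk. It does not remove the point, because the visit list itself gives BMT no early study contact and an analysis plan cannot supply data that were never collected.

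The patient is not the only informant. Each needs a caregiver with contact about twice a week on average, who attends follow-up visits. This stands too: it argues for the longer half-lives and smaller ratios.

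A reader might extend the concern to all harms. Hospitalization and nursing-home admission can be recovered at weeks 15, 30 and 52. Falls are a separate outcome with a three-month window. Neuropsychiatric change is measured by questionnaires, although these would not catch every transient episode. The point is therefore confined to non-serious, transient events.

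The analysis of adverse events is normally left to the analysis plan, and the article calls the weighing of safety against benefit exploratory. That limits the weight of the point, but the asymmetry lies in the stated schedule.

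Finally, a reader might conclude that events found at Visit 2 or during the surgical stay should be left out of the comparison. That would be wrong: some of them are real harm from DBS, and removing them could hide it. The post-surgical check is also part of the intervention and should stay.

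**Conclusion.** The point holds as a risk of differential ascertainment, limited to non-serious, transient adverse events. The likely direction is against DBS: it would look less safe than it is, not falsely safe. The unequal contact (2 against 1 up to week 15, 4 against 3 up to week 52, plus the stay and clinic visits) comes from the text. The size does not. The spurious ratios of about 1.14 to 1.55 for Visit 2 in weeks 0-15 rest wholly on the assumed recall half-life, surgery date and constant event rate, and that window shows the effect at its largest. Over 30 or 52 weeks it is smaller, and at a 26-week half-life it nearly vanishes. The primary endpoint and the sample size are unaffected. It is worth correcting because the remedy is cheap and the safety comparison is meant to inform a larger trial.

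**What to change.** 1. At weeks 15, 30 and 52, put the same scripted adverse-event question to patient and caregiver in both arms, covering the full interval since the last common visit.
2. Record the source visit of each event (common visit, Visit 2, surgical stay, programming visit, other).
3. Compare serious adverse events between the arms. For non-serious events, report the all-event comparison together with one restricted to events elicited at the common visits. Flag, without excluding, events first noted at Visit 2, during the surgical stay or at programming visits.
4. For patients still to be enrolled, add one scripted adverse-event telephone call to BMT patients, at a fixed week after randomization that matches the expected timing of Visit 2.

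The cost is a short script, one extra field in the existing database, analysis-plan wording and at most 22 short calls (22 patients are planned for the BMT arm); the call needs a minor amendment. The restricted comparison uses fewer DBS events, which is why it accompanies the all-event comparison and does not replace it.
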